Surveys have repeatedly found overwhelming support for ADs, whether communicated in writing or more informally through conversations with families and health professionals [17,18]. Major professional organizations also support advance planning for health care and research [19-21]. Widespread endorsement of ADs is due to their potential to preserve patient autonomy, improve end-of-life medical care, alleviate the burden of substitute decision-making for loved ones, reduce stress, anxiety and depression in surviving relatives, and limit the use of unwanted forms of life-support. ADs may also result in more cost-effective health care by discouraging physicians from resorting to unwanted treatment [17,18,22,23].

Despite widespread professional and public endorsement of ADs for health care, still too few people actually execute them or even discuss future treatment wishes with loved ones or healthcare practitioners [2,18,22,24,25]. The most common reasons include trusting family members to make the right decision when the time comes, the tendency to defer end-of-life planning until facing a life-threatening illness, a lack of knowledge about ADs, and limited access to needed forms [11]. According to our own survey [25], even fewer have voiced their wishes in relation to research involvement. Interestingly, survey participants who had done so were more likely to have conveyed their preferences for care. Accordingly, dedicating a section of AD forms to the person's wishes regarding health research participation could prove effective in increasing the frequency of prospective authorization for research participation [26,27].

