### The research objectives

The purpose of this trial is to assess the efficacy of a multimodal professionally-led advance planning intervention in 1) improving the accuracy of substitute decision-making (primary outcome) and 2) increasing the frequency of written ADs for health care and research (secondary outcome). Given current knowledge, the tested intervention includes an educational component on ADs and stimulates discussion between an older adult and his/her self-selected proxy with respect to end-of-life care and research participation. The study incorporates a cost analysis to measure public savings that result from improving proxy predictions of preferences.

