■ videos showing people sharing their experiences (e.g., a person expressing difficulties due to not knowing the wishes of a loved one, a physician explaining the importance of advance planning for health care) or explaining how to use *My Preferences *to convey their wishes to family members,

■ activities encouraging participants to express their own point of view and to start completing *My Preferences *which then serves as an external memory aid to help overcome deficits in memory processes that are frequent among older adults.

At the third and final meeting, the social worker checks subjects' understanding of the information delivered at the group session, explains any terms in *My Preferences *that are still unfamiliar to the participants, and assists older adults in filling one out if desired. Those who elect to complete *My Preferences *at this stage are advised to inform family members and designated substitute decision-makers of its location and content. The social worker then requests a copy for analysis purposes. Content analyses of completed guides will allow us to determine whether the older adult designated a substitute decision-maker and/or expressed preferences regarding health care and research participation. Lastly, the social worker explores participants' satisfaction with the process and collects any suggestions they might have on how to improve the intervention.

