### Primary and secondary outcome measures

Prediction accuracy of substitute decision-making is the primary outcome and rate of completed guides, the secondary outcome. Concordance is the most important outcome of advance planning activities. However, we consider important to also measure the rate of documented preferences as these could raise less controversy in the event of incompetence than oral instructions given only to a single family member.

Concordance assessments are repeated at the end of the intervention (first posttest) and 6 months later (second posttest), according to the same procedure as at baseline. However, the first posttest uses new sets of treatments, sudden health events and research protocols to counter recall bias. Older adults' decisions under these various scenarios, and their proxies' predictions concerning those decisions, are recorded by the same research nurses who interviewed them at baseline. The second posttest will allow us to determine whether the positive effect of the intervention on prediction accuracy, if any, is maintained for at least six months. Copies of completed *My Preferences *are made at the first posttest and, for those who have yet to complete one, at the second posttest. Allocating six months to fill out *My Preferences *gives participants extra time to decide whether they want to commit directives in writing. A longer interval carries the risk of losing too many participants and no longer permits attributing the observed effect to the intervention, as opposed to more recent events that might have occurred in the meantime. Evidence regarding the impact of the intervention on the rate of completed guides will be based on written documents rather than self-report as the latter was found to overestimate true completion rates [39].

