### Statistical analyses

Persons who decline participation or drop out will be compared to trial participants with parametric or non-parametric two-sample tests (depending on the distribution of the data) and results used to judge the scope of study findings. The same tests will be used to compare participants' baseline characteristics across study groups. Potential confounders and compliance indices will be candidates for adjustment when testing the impact of the intervention on the outcome measures [82]. All analyses will be based on allocation to the intervention or control group (i.e. by intention-to-treat). To account for losses to follow-up, analyses will be conducted in duplicate, first restricting the sample to the dyads for which we have complete follow-up data, then using a conservative approach by which dyads that do not provide such data are assumed not to have documented preferences and their baseline concordance levels are used for imputation [83].

The primary analysis will involve calculating composite scores of agreement across health states for each dyad. Calculations will generate a total concordance score as well as sub-scores derived from restricting summations to the clinical or research vignettes. Growth-curve modeling implemented with SAS PROC MIXED will be used to compare composite scores across time points and groups, an approach that accounts for the within-dyad correlation over time and accommodates missing values [84,85]. To further elucidate the impact of the intervention, secondary analyses will involve applying the same statistical procedure to the concordance sub-scores. A multivariable logistic model will be used to compare group-specific completion rates of *My Preferences *6 months post-intervention. The financial impact of the intervention will be investigated with Student's *t *test for independent samples or its non-parametric equivalent.

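### The secondary objective covers written directives for health care and for research, but a single guide-completion rate is the only comparison planned, and it cannot by itself support a conclusion about research directives

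*Protocol article*

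**What the plan says.** The Research objectives section gives the second aim as "increasing the frequency of written ADs for health care and research (secondary outcome"). Under Primary and secondary outcome measures this becomes "rate of completed guides, the secondary outcome". The reason given there is that "we consider important to also measure the rate of documented preferences". Under Statistical analyses there is one comparison: "A multivariable logistic model will be used to compare group-specific completion rates of" the guide, 6 months post-intervention. The same section splits the primary outcome into clinical and research sub-scores and applies the same model to each. It gives no such split for documentation.

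The guide covers three things: naming substitute decision-makers, health care wishes and research wishes (Intervention in the experimental group). That section plans a content analysis of completed guides to establish "whether the older adult designated a substitute decision-maker and/or expressed preferences regarding health care and research participation". The article does not tie this analysis to the outcome or the model.

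Copies of completed guides are "made at the first posttest and, for those who have yet to complete one, at the second posttest".

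**The concern.** The objective names two kinds of directive and the test counts one event. Because of the and/or in the content-analysis sentence, a guide may count as completed with its research part blank. A positive completion result driven by health care wishes or by naming a substitute could then be reported as success on research directives without evidence for it.

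This matters because documentation is the trial's only measure of written research directives. The Discussion intends the documentation estimates to inform whether family consent should carry over to research. The Background gives some reason to expect a gap between the two kinds of wishes: in the investigators' own survey, "even fewer have voiced their wishes in relation to research involvement".

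The copying rule adds a smaller problem in the opposite direction. If a guide counts as complete at the first posttest with its research part blank, a research section added in the next 6 months is not seen, although the model concerns status at 6 months.

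**Working it through.** **1. Can one yes/no event return both frequencies?** Take four possible guides and three readings of completed. The third reading, preferences written down, is suggested by the wording of the outcome section, the follow-up section, the imputation rule and the Table 1 title. A health care directive follows the definition in The potential value of advance planning: treatment preferences and/or a designated person.

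| Guide | Any part filled | Every part filled | Preferences written | Health care directive | Research preferences |
|---|---|---|---|---|---|
| A: substitute named only | yes | no | no | yes | no |
| B: substitute and care wishes, research blank | yes | no | yes | yes | no |
| C: all parts | yes | yes | yes | yes | yes |
| D: research wishes only | yes | no | yes | no | yes |

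No reading reproduces the research column. Any part filled counts A and B falsely, every part filled misses D, and preferences written counts B falsely. For health care, any part filled is wrong only on D.

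**2. Reproducing Table 1.** Inputs: n = 86 per group and two-sided α = 0.05. Rows 1 and 2 use a control rate of 0.12 with odds ratios of 4.0 and 3.7; row 3 uses 0.23 against 0.48.

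Experimental rate, row 1: odds = 4.0 × 0.12/0.88 = 0.5455, so p = 0.5455/1.5455 = 0.353. Row 2 in the same way: 0.335.

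Power = Φ{[|p1 − p2| − 1.96 √(2p̄(1 − p̄)/n)] / √[(p1(1 − p1) + p2(1 − p2))/n]}, where p̄ is the mean of p1 and p2.

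Row 1: (0.2329 − 0.1270)/0.0623 = 1.70, giving 95.5%. Rows 2 and 3 give 92.7% and 93.6%. The stated values are 95%, 92% and 93%, so all three reproduce.

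**3. What those figures refer to.** Row 1 comes from the investigators' review of directives for health care. Row 3 comes from the trial in veteran outpatients, described in the discussion of health care preferences. The article does not describe the row 2 source, but its control rate is borrowed from the same review. None is presented as power for research directives.

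**4. Illustration for research directives.** Assumption, not in the article: a share s of completed guides contains research preferences, the same in both arms. Both row 1 rates are multiplied by s. The overstatement factor is 1/s, and the guides counted without research preferences are 86 × p × (1 − s).

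| s | Control | Experimental | Factor 1/s | Excess guides per 86 (control, experimental) | Power |
|---|---|---|---|---|---|
| 1.0 | 0.120 | 0.353 | 1.00 | 0, 0 | 95.5% |
| 0.9 | 0.108 | 0.318 | 1.11 | 1.0, 3.0 | 92.6% |
| 0.8 | 0.096 | 0.282 | 1.25 | 2.1, 6.1 | 88.4% |
| 0.7 | 0.084 | 0.247 | 1.43 | 3.1, 9.1 | 82.6% |
| 0.5 | 0.060 | 0.176 | 2.00 | 5.2, 15.2 | 66.0% |

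At s = 0.5, rows 2 and 3 give 60.5% and 57.4%. The equal-share assumption keeps the risk ratio at 0.353/0.12 = 2.94 by construction. Unequal shares would change it.

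**The case against.** The strongest reply is that the data for the split will exist, because the content analysis is planned, and that a one-sentence account of a model in a condensed article does not rule out using it. The full protocol or analysis plan may also define completed. This stands in part: the missing definition is not the finding. But the article does name the outcome and its test, and step 1 shows that none of the readings it suggests makes that single event measure research directives.

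A second reply is that the objective can be read as one document with an extended purpose. That is possible, but a completion rate would then support a statement about the guide, still not about research wishes.

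A reader might infer that health care directives are miscounted too. The article does not support this in general: by its own Background definition, a guide that only names a substitute is a written health care directive. Such a guide is not a documented preference in the sense of the outcome section and Table 1, so the terms conflict, but that is a matter for reconciliation.

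The evidence on the size of the gap is mixed. The survey concerned wishes voiced without this guide. The Background also suggests that a dedicated research section could raise research authorization, and Potential limitations says that participants may favor research directives in particular.

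The copying criticism is conditional. If completed means every part filled, a guide with a blank research section is still incomplete and would be copied at the second posttest.

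**Conclusion.** The point holds for research directives. The stated outcome and its only between-arm test cannot alone support a conclusion about them, and the completion rate can overcount them. A program could not recover the research frequency from the completion indicator; it needs the content analysis.

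The size is unknown. The range in step 4 rests on an assumed blank share, equal in both arms, and is not an estimate. Power stays above 80% unless more than 30% of completed guides lack research preferences (row 1), so it would be wrong to read this as showing that the research comparison is underpowered. It would also be wrong to read it as an error in Table 1, whose figures reproduce. Table 1 simply shows no power for research directives. The loss of late-added sections through the copying rule applies only under the looser readings of completed.

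The change should be made, because it concerns one of the two named targets of the secondary objective and uses material already being collected.

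**What to change.** - Use the planned content analysis to define two yes/no events at 6 months: a written health care directive, by the Background definition, and research preferences documented. Fit the planned logistic model to each, mirroring the clinical and research split of the primary outcome. Apply the existing non-event rule for dyads without data to both.
- Base any conclusion on research directives only on the research event. Report guide completion and substitute designation descriptively.
- Reconcile the terms written directive, completed guide and documented preferences across the Background, the intervention section and the outcome section.
- State beside Table 1 that at least rows 1 and 3 rest on health care directive rates and that no power is shown for research directives.
- At the second posttest, re-check and re-copy guides already copied at the first, so that sections added later are counted.

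The cost is one additional secondary test, with a statement of how the two are to be interpreted together, and a few minutes of copying at an existing visit. The sample size does not change.

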### Cost Analysis

To measure the intervention's financial impact, we will use the goals of care chosen by the older adults and their proxies at baseline and at the second posttest for the various health events. These goals of care will have been transformed into costs previously. The differential cost between the decisions made at baseline by the older adults in the experimental group and those made by their proxies for all scenarios will be deducted from the differential cost at posttest 2. To establish the net effect, the results will be compared with those of the control group calculated with the same method.

Three steps are required to cost each of the possible healthcare scenarios (health states × goals of care × health events): 1) identifying the healthcare resources required; 2) measuring the amount of resources previously identified; and 3) costing each resource [67,68].

As in previous studies [53,69,70], to identify the resources to be costed, we considered the health care and services that could be influenced by the preferences of the older adults or their proxies and could thus generate different costs. Therefore, we will value the healthcare services delivered essentially by the public healthcare system: hospital stays, nursing and assisted care, general and specialized medical care, ambulance transportation and other direct or indirect treatment-related costs. We will disregard healthcare services provided by family members on a volunteer basis.

To determine the number of resources required, we asked three physicians to create a treatment profile for each scenario, which were later validated from existing care protocols [71-78]. Relying on their expertise and experience, the physicians established a list of healthcare services based on the most frequent situations in their practice for cases similar to the various scenarios provided. These treatment profiles therefore combine a number of healthcare services to make up a "typical" treatment for each scenario in the study.

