### Sample size

We are aiming for 86 dyads per group at study completion, which would provide 80% power to detect a standardized difference of 0.43 in overall prediction accuracy between the study groups (calculation based on the *t *statistic, two-sided α = 0.05, nQuery Advisor 6.0). The expected standardized difference was derived from Schwartz *et al*. [31] whose study resembles our own in many respects. The tested interventions are of comparable intensity and duration. Both include an AD educational component and devote a central role to proxies. Moreover, in both cases, prediction accuracy is measured with a composite index derived from combining proxy's ability to predict the older adult's preferences under various hypothetical scenarios.

Accounting for a drop-out rate of 10% at posttest 1 and 20% at posttest 2, 240 dyads will be randomized. As indicated in Figure 1, we started the recruitment process with a random list of 1,000 individuals who fulfill our first four inclusion criteria. This number should allow us to reach the target sample size, further accounting for sampled individuals who will be found ineligible (e.g., institutionalized or deceased, no longer reside in the study area, no proxy meeting study criteria), refuse to be interviewed, or decline study participation.

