**Figure 1 F1:**
[figure not shown]
**Study subjects flow chart (with estimated sample sizes in parentheses)**.

The above calculations assume that we will compare groups on posttest mean concordance scores as this allowed us to use the best available estimate of the likely effect of the intervention. However, our design involves repeated measurements of concordance over time that will be analyzed by growth-curve modeling, a more sophisticated approach that effectively uses all the available time points to estimate individual trajectories. Determination of suitable sample sizes for multilevel analyses is complex, in part because explicit formulas have not yet been derived for general models. However, simulations by Mass & Hox [86] show that between 50 and 100 units per group are needed to justify claims as to the absence of bias in standard error estimates. As shown in Figure 1, projected sample sizes are 120 units per group at baseline, 108 at posttest 1 and 86 at study completion. Since all data will contribute to some extent in estimating the model parameters, our approach to sample size estimation is conservative and protects against an underpowered study.

Lastly, as shown in Table 1, 86 dyads per group also provide sufficient power to detect a meaningful difference between groups for the secondary outcome.

**Table 1 T1:** Power to detect the intervention effect on documented preferences, according to three sources of information (*n *= 86 dyads per group, two-sided α = 0.05)

Source	Odds ratio (95% CI)	Event rate in the Control group	Event rate in the Experimental group	Power
Bravo *et al*. [39]	4.0 (1.6 - 10.4)	0.12*		95%
Patel *et al*. [87]	3.7 (1.5 - 9.4)	0.12*		92%
Pearlman *et al*. [10]		0.23	0.48	93%

* Derived from 13 RCTs included in our systematic review (mean = 0.12, sd = 0.182, range: 0 to 0.56) and applied to Patel *et al*. who did not report the mean event rate across control groups.

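### The cost comparison rests on an unadjusted change score; adjusting for the baseline cost differential would be more precise and would guard against baseline-related dropout

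*Protocol article*

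**What the plan says.** The Cost Analysis section converts the goals of care chosen at baseline and at the second posttest into costs. It takes the older adult-proxy cost difference at each of the two visits; the baseline difference "for all scenarios will be deducted from the differential cost at posttest 2", and the result is compared with that of the control group. Posttest 1 plays no part.

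The Statistical analyses section names the test: "The financial impact of the intervention will be investigated with Student's" t test for independent samples, or its non-parametric equivalent. Neither takes a covariate.

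The same section has a two-part rule for losses to follow-up. All analyses are first run on dyads with complete follow-up. They are then repeated with a conservative imputation in which "dyads that do not provide such data are assumed not to have documented preferences and their baseline concordance levels are used for imputation". The second part names documentation and concordance, not cost.

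The Sample size section expects that "projected sample sizes are 120 units per group at baseline, 108 at posttest 1 and 86 at study completion". Baseline concordance is assessed before randomization (Recruitment process).

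**The concern.** The baseline cost differential is measured before randomization and is likely to predict the posttest 2 differential. Subtracting it in full fixes the slope on baseline at 1. A fitted slope is usually well below 1, and forcing it to 1 adds noise to the arm comparison.

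A fixed slope of 1 also leaves regression to the mean in the change score. That is harmless when the arms are balanced on baseline. It is not harmless if the dyads still present at posttest 2 have different baseline differentials in the two arms. The arms receive visibly different programmes (home visits and a group session against group workshops only), and 28% of dyads are expected to be gone by posttest 2, so this is possible. Regression to the mean could then look like a saving or a cost of the intervention. Savings to the healthcare system are a stated aim of the trial.

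**Working it through.** **1. The plan's own figures.** Inputs from the Sample size section are a standardized difference of 0.43, two-sided α of 0.05, 86 dyads per group at completion and 240 randomized.
- The noncentral t distribution gives 80.06% power at 86 per group and 79.6% at 85, so 86 is reproduced.
- Retention: 120 × 0.9 = 108, and 108 × 0.8 = 86.4. In reverse, 86/0.72 = 119.4, so 120 per group and 240 in all.
- Without posttest 2: 120 − 86 = 34 per arm, 34/120 = 28.3%, or 68 of 240.

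**2. Precision among dyads with posttest 2.** Let s be the SD of the cost differential, taken as equal at the two visits (an assumption), and r the baseline-to-posttest 2 correlation (not given, so shown as a range).
- Change-score variance: 2(1−r)s².
- Baseline-adjusted variance: (1−r²)s².
- Ratio, adjusted to change score: (1−r²)/[2(1−r)] = (1+r)/2, a reduction of (1−r)/2.

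| r | Reduction in variance | 86 change-score dyads per arm are worth, in adjusted dyads | Power, change score | Power, adjusted |
|---|---|---|---|---|
| 0.3 | 35% | 56 | 66% | 84% |
| 0.5 | 25% | 65 | 80% | 90% |
| 0.7 | 15% | 73 | 95% | 98% |
| 0.9 | 5% | 82 | about 100% | about 100% |

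The third column is 86 × (1+r)/2. The power columns use 86 per arm and an effect of 0.43 SD of the posttest 2 differential. That effect is borrowed from prediction accuracy, because the article states none for cost, so these columns are illustrative only.

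**3. Bias when dropout depends on baseline in one arm.** 4,000 trials per setting were simulated with 120 dyads per arm, unit SDs and no true effect. The assumed log-odds of staying to posttest 2 were 1.0 in one arm and 1.0 − 0.7 × baseline (in SD units) in the other. Overall retention was 72%, matching the plan.
- False effect, completers' change score: 0.128, 0.092 and 0.054 SD at r = 0.3, 0.5 and 0.7.
- False effect, baseline-adjusted: 0.002 SD or less in size.
- In a separate run of the same design, type I error of the change-score test was about 11%, 9% and 8%, against about 5% for the adjusted analysis.

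The pattern is regression to the mean. The bias is (1−r) times the shift in the completers' baseline mean in the affected arm: 0.128/0.7, 0.092/0.5 and 0.054/0.3 each give about 0.18 SD.

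**4. If baseline carry-forward were extended to cost.** Each dyad without posttest 2 would have a change of exactly zero. With equal retention in the arms, the estimated effect becomes 86/120 = 0.72 of its value in completers; for example 0.43 × 86/120 = 0.31.

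**5. Do the 68 baseline-only dyads add information?** In a two-visit likelihood model with a common baseline mean and covariance, the likelihood splits into a part for baseline and a part for posttest 2 given baseline. The arm effect sits only in the second part, which only dyads with posttest 2 inform. Fits to three simulated trials agreed: the arm effect equalled that of completers-only analysis of covariance (0.79970, 0.49194, 0.46079) and did not move when the baseline-only dyads were deleted.

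**The case against.** Several points on the other side stand.

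- **The named test is not invalid.** Under random dropout the change-score t test is unbiased and keeps its error rate.
- **The plan has a rule for missing cost data.** The complete-case half of the loss rule is general. A reader might infer that nothing is laid down for the 28% without posttest 2; the text does not support that. Carry-forward of costs is likewise a step the plan never states, so its dilution is a reason to rule it out and not a fault in what is written.
- **The baselines of all 240 dyads are not a lost resource.** A reader might infer that the t test discards usable information on 68 dyads. The change score already uses baseline for the 172 expected completers, and the other 68 add nothing to the arm effect even in a two-visit mixed model (step 5).
- **The gain may be small.** Only the first posttest is said to use new sets of treatments, events and protocols, so baseline and posttest 2 apparently share scenarios and r could be high. At r = 0.9 the saving in variance is 5%.
- **The bias figures rest on an assumed mechanism.** The article gives no reason to expect that particular strength, or dropout tied to baseline in one arm only.

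One point stands only in part. The Statistical analyses section makes potential confounders candidates for adjustment, and an analysis plan not shown may add detail. But the article does name a test for cost, and that test cannot adjust for anything.

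**Conclusion.** The concern holds as a point of modest importance. The article fixes an unadjusted comparison of change scores for cost, in practice among about 86 dyads per arm. Adjusting for the baseline differential in the same dyads would lower the variance by (1−r)/2, or 35% to 5% for r from 0.3 to 0.9. It would also remove bias from dropout that depends on baseline differently by arm, put at about 0.13 to 0.05 SD for r from 0.3 to 0.7 under the assumed mechanism. It would not cure dropout that depends on the unseen posttest 2 result.

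These sizes rest on equal SDs at the two visits, an assumed r and an assumed dropout model. The primary and secondary analyses and the sample size are unaffected.

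**What to change.** In the Statistical analyses section, replace the two-sample test for cost with a linear model of the posttest 2 cost differential on arm, the baseline cost differential and the two stratification factors (type of proxy; prior documentation of healthcare preferences), fitted to dyads with posttest 2. Use robust or bootstrap standard errors to deal with skewness; the result remains a mean difference in dollars.

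State that the baseline-carried-forward imputation is not extended to costs, because it would set the change to zero for about 28% of dyads.

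The cost is a change of wording, best made before outcome data are seen. All inputs are already collected, and neither sample size nor procedures change.

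### The non-parametric option for the cost analysis would, on its usual reading, not test mean savings, which is what that analysis sets out to measure

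*Protocol article*

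**What the plan says.** The research objectives section gives the purpose: "The study incorporates a cost analysis to measure public savings that result from improving proxy predictions of preferences".

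The Cost Analysis section defines the variable. It starts from "The differential cost between the decisions made at baseline by the older adults in the experimental group and those made by their proxies", taken over all scenarios. This baseline differential is deducted from the same differential at posttest 2. The between-arm contrast follows: "To establish the net effect, the results will be compared with those of the control group calculated with the same method". Resource costs are set in 2010 dollars, so the quantity is in money.

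The Statistical analyses section then names the test: Student's t "test for independent samples or its non-parametric equivalent". It does not say which non-parametric test is meant or when it would replace the t test. The only selection rule nearby, "depending on the distribution of the data", is attached to comparisons of refusers, drop-outs and baseline characteristics, not to costs.

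**The concern.** A public payer's saving is the mean saving per person multiplied by the number of people. The t test addresses the difference in means. The Mann-Whitney test addresses whether a randomly chosen dyad in one arm tends to have a larger value than one in the other. The two agree when the arms differ only by a shift. They can part company when the distributions are skewed and differ in shape.

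A difference in shape is plausible here. An intervention that aligns proxies with older adults would alter the spread of the differentials, and the share that are zero, in one arm only. Goals of care run from palliative to intensive, so a single changed choice could move cost a good deal.

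At stake is the financial conclusion. A significant rank test would not by itself show that mean savings differ, and a non-significant one would not show that they are similar. Nothing else in the article fixes the mean difference as the basis of inference.

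**Working it through.** **Inputs**
- 86 dyads per group at completion (Sample size section).
- Two-sided α = 0.05, stated there for the primary outcome and assumed here for the cost test.
- No mean, SD or distribution of cost is given, so every shape below is an assumption and a range is shown.
- The non-parametric test is taken to be Mann-Whitney, also an assumption.

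**Step 1. Reproduce the plan's own figure.** With a standardized difference of 0.43 and 80% power:

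n = 2(1.960 + 0.842)² / 0.43² = 2 × 7.85 / 0.1849 = 84.9, so 85 per group by the normal approximation.

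The exact t calculation gives 85.87, so 86, with power 80.06%. Attrition: 120 × 0.90 = 108 and 108 × 0.80 = 86.4. The stated 86 reproduces. It was set for prediction accuracy, not costs, and serves here only as the n.

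**Step 2. What each test targets.** The t test's null is E(X) = E(Y). Mann-Whitney is centred on P(X > Y) + ½P(X = Y) = ½. For two lognormal variables with the same mean and log-SDs s₁ and s₂:

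P(X > Y) = Φ{ [(s₂² − s₁²)/2] / √(s₁² + s₂²) }

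- 0.8 and 1.0: Φ(0.18/1.281) = Φ(0.141) = 0.556
- 0.5 and 1.0: Φ(0.375/1.118) = Φ(0.335) = 0.631
- 0.75 and 1.25: Φ(0.5/1.458) = Φ(0.343) = 0.634

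The means are equal, yet none of these is 0.5, so a rank test will reject more often than 5%.

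**Step 3. Rejection rates with equal means** (86 per arm, 20,000 simulated trials per row). In the mostly-zero rows a share p of dyads has a saving averaging 1/p (lognormal, log-SD 0.5) and the rest have zero, so the mean saving is 1 in both arms.

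| Assumed shape | Mann-Whitney | Student t |
|---|---|---|
| Lognormal, log-SD 1.0 / 1.0 (identical) | 5.1% | 4.7% |
| Lognormal 0.8 / 1.0 | 24.6% | 5.3% |
| Lognormal 0.5 / 1.0 | 84.6% | 7.3% |
| Lognormal 0.75 / 1.25 | 86.4% | 7.5% |
| Lognormal 0.5 / 1.25 (extreme) | 98.8% | 9.8% |
| Mostly zero, p = 20% / 20% | 4.9% | 4.9% |
| Mostly zero, p = 30% / 20% | 20.6% | 5.6% |
| Mostly zero, p = 30% / 15% | 46.4% | 5.2% |
| Mostly zero, p = 40% / 20% | 53.9% | 5.5% |
| Mostly zero, p = 40% / 10% (extreme) | 97.8% | 7.3% |
| Normal, SD ratio 1 to 2 | 5.2-5.9% | 5.2-5.3% |

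Welch's t was within 0.1 percentage points of Student's t in every row.

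**Step 4. A variable closer to the article's.** The Cost Analysis differential is signed and runs over 4 health states × 3 health events = 12 scenarios. Assumed: goal-of-care costs between 3,000 and 60,000, and 70% or 90% of answers persisting. With unbiased proxy errors the means are equal and only the spread changes. Mann-Whitney then rejected in 4.6-8.0% of trials and Student's t in 4.2-5.1%.

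**Step 5. The converse.** Two lognormals with equal medians and log-SDs 0.5 and 1.0 have a mean ratio of exp[(1.0² − 0.5²)/2] = exp(0.375) = 1.45. Mann-Whitney detected this 45% difference in means in 5.4% of trials, Student's t in 64.1%.

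**The case against.** The strongest reply has four parts.

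1. The article never names Mann-Whitney. A permutation or bootstrap test of the mean difference is also non-parametric, and a condensed article may leave that choice to the analysis plan.
2. The cost variable is a signed difference of differences over 12 scenarios, not ordinary right-skewed cost data. Step 4 shows that a rank test can then behave almost as the t test does. With real mean effects and proxies erring toward dearer care, the two tests had nearly the same power (34% and 33%, 83% and 81%, 61% and 59%, 96% and 95%). With proxies erring toward cheaper care they differed by 13 points (39% and 52%, 61% and 74%).
3. Naming a test does not stop the authors from reporting the dollar difference with an interval.
4. A change score is unbiased under randomization, and the article already makes confounders candidates for adjustment.

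The second part stands and limits the size of the problem. The third and fourth also stand: the article does not rule out a dollar estimate, and subtracting baseline is a matter of precision, not bias. The first stands only in part. The article does fix the pair of options, and the usual reading of the second is a rank test. Leaving it open allows an analysis that does not address the stated aim.

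**Conclusion.** The point holds as a mismatch between aim and test. The aim is a mean-based money quantity, and the permitted alternative, on its usual reading, does not test it. With equal means at 86 per arm, the rank test's rejection rate is about 5-8% for near-symmetric signed differentials. It is about 20-85% for skewed arms of moderately different shape, and higher only in extreme constructions. This rests on the Mann-Whitney reading and on assumed distributions. Inflation needs skew together with a difference in shape.

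A reader might infer more than the article supports:
- **That a false financial finding is near certain.** Rates of 95% or more come only from extreme shapes, and nothing in the article says costs take them.
- **That the costs will be mostly zeros with a few very large values.** This is plausible but is not stated.
- **That the test will be chosen after seeing the data.** No selection rule for costs is given. The distribution-based rule is written for other comparisons.
- **That the trial's main results are in doubt.** Prediction accuracy and completion of the guide have their own analyses and are untouched.

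**What to change.** In the Statistical analyses section, delete the non-parametric alternative from the sentence on financial impact. State instead that inference rests on the between-arm difference in mean net cost as the Cost Analysis section defines it (older adult-proxy cost differential, posttest 2 against baseline). Give a 95% confidence interval, either Welch's or from a bootstrap that resamples dyads within arm.

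Preferably, for precision, regress the posttest 2 differential on arm, baseline differential and the two stratification factors (type of proxy, prior documentation of preferences). The outcome in that model must be the older adult-proxy differential, not posttest 2 cost alone. Any rank test can be kept as supportive.

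The cost is one or two sentences and, if chosen, a short bootstrap routine. No new data are needed, and the sample size and the other analyses do not change.
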